## Abstract

**Background:**

This study will evaluate hypoxia, as a novel concept in the pathogenesis of diabetic macular oedema (DMO). As the oxygen demand of the eye is maximum during dark-adaptation, we hypothesize that wearing light-masks during sleep will cause regression and prevent the development and progression of DMO. The study protocol comprises both an efficacy and mechanistic evaluation to test this hypothesis.

**Method/Design:**

This is a phase III randomised controlled single-masked multicentre clinical trial to test the clinical efficacy of light-masks at preventing dark-adaptation in the treatment of non-central DMO. Three hundred patients with non-centre-involving DMO in at least one eye will be randomised 1:1 to light-masks and control masks (with no light) to be used during sleep at night for a period of 24 months. The primary outcome is regression of non-central oedema by assessing change in the zone of maximal retinal thickness at baseline on optical coherence tomography (SD-OCT). Secondary outcomes will evaluate the prevention of development and progression of DMO by assessing changes in retinal thickness in different regions of the macula, macular volume, refracted visual acuity and level of retinopathy. Safety parameters will include sleep disturbance. Adverse events and measures of compliance will be assessed over 24 months. Participants recruited to the mechanistic sub-study will have additional retinal oximetry, multifocal electroretinography (ERG) and microperimetry to evaluate the role of hypoxia by assessing and comparing changes induced by supplemental oxygen and the light-masks at 12 months.

**Discussion:**

The outcomes of this study will provide insight into the pathogenesis of DMO and provide evidence on whether a simple, non-invasive device in the form of a light-mask can help prevent the progression to centre-involving DMO and visual impairment in people with diabetes.

## Background

Diabetic retinopathy is the most common complication of diabetes. Diabetic macular oedema (DMO), characterised by leakage of fluid from compromised blood vessels in the central retina, is the most frequent cause of visual impairment in people with diabetes. DMO may be central or non-central oedema. Non-central oedema does not usually affect visual acuity. When it affects the central 1 mm of the macula, it causes visual impairment. Over 30% of eyes with untreated centre-involving macular oedema lose 3 or more lines of vision by 5 years
[1].

Patients with non-central DMO are monitored with slit-lamp biomicroscopy and spectral domain optical coherence tomography (SD-OCT) every 4 to 6 months for progression to centre-involving DMO. SD-OCT provides information on the changes in the retinal thickness and morphology of the retina due to DMO. Approximately 30% of these patients progress to centre-involving macular oedema by 12 months
[2].

Treatment is available only when the DMO becomes clinically significant or shows progression to the centre. Laser treatment is the standard of care when the DMO becomes clinically significant. Although laser treatment reduces the risk of moderate visual loss by 50% at this stage, it is not effective in restoring visual acuity and has significant side effects that impact on the quality of life of these people
[1]. Newer treatment options of injections of vascular endothelial growth factor (VEGF) inhibitors are also available but only for centre-involving DMO. These treatments are costly and cause significant burden to the patient, their caregivers and the healthcare system
[3, 4].

There are no treatment options for non-clinically significant DMO except optimal control of diabetes and hypertension. Laser photocoagulation may be performed for non-central clinically significant macular oedema. The natural history of the disease is to progress from non-central to centre-involving DMO
[2]. Therefore, there is a substantial unmet need for both treatment and prevention of progression of non-centre-involving DMO.

The exact pathogenesis of diabetic retinopathy and DMO is uncertain. The rationale for this study is that increased glucose is associated in various ways with a decrease in oxygen supply to the retina, and an increase in oxygen demand
[5]. This leads to increased hypoxia, and an overproduction of VEGF, which damages the circulation, and in doing so will further decrease retinal oxygen supply in a vicious circle. Only at such a stage will all the other known mechanisms that contribute to retinal vascular damage operate and contribute to the various clinical features of diabetic retinopathy. Rods use more oxygen than any other cell in the body
[5, 6]. Oxygen is required to support the extreme sensitivity to light that develops during dark-adaptation. As a result, the oxygen tension in the mitochondrial region of the rods in darkness falls to zero. The exact mechanism is that in darkness the rod outer segment membrane becomes extremely permeable to ions and water, which enter the cell and are pumped out in the inner segment
[7]. The resulting ‘dark current’ is large and requires all the oxygen available in the normal eye
[8–10]. If retinal circulation is compromised in any way, the hypoxia present in the outer retina increases and spreads into the inner part.

Arden hypothesized that if dark-adaptation was prevented, the rod dark current would never become maximal and diabetic retinopathy would be alleviated by decreasing the oxygen demand
[8, 9]. Since people only dark-adapt at night during sleep, sleeping in an illuminated environment should prevent or reverse the condition. In clinical trials it is important to provide uniform illumination to each patient, so we have made ‘light-masks’ containing organic light emitting diodes to illuminate the closed eyelids during sleep. Sufficient low intensity light is transmitted by the lids to reduce the dark current allowing the quantity of light can be measured. It is also important that the masks are comfortable to wear and do not disturb sleep.

The relationship of these SD-OCT changes in retinal morphology and thickness to hypoxia has not been determined. Similarly, the relation of the visual function to hypoxia also remains unclear. This is the subject of the mechanistic investigation.

### Objectives

The primary objective of the study is to explore whether wearing light-masks during sleep at night reduces, relative to the control masks, the maximal zone macular thickness at baseline as measured by SD-OCT in the study eye of patients with non-centre-involving DMO at 24 months.

Secondary objectives include whether the effect of light-masks, relative to control masks, can prevent the progression of non-centre-involving DMO by assessing the changes in retinal thickness in each region of the macula, macular volume, macular morphology, retinopathy status, visual acuity and proportion of patients requiring rescue laser or anti-VEGF treatment at 12 and 24 months. The safety and tolerability of the masks will be assessed and will include measures of compliance and questionnaires to assess the effect of the masks on sleep.

The mechanistic evaluation will explore and compare the changes in retinal function induced by supplemental oxygen and light-mask on multifocal ERG (inner retina) and scotopic microperimetry (outer retina) at 12 months. The changes in oxygen saturation in the retinal vessels will be assessed by retinal oximetry using the Oxymap T1 Retinal Oximeter (Oxymap Analyzer v.2.4.2, Reykjavik, Iceland

## Methods/Design

This is a phase III randomised controlled single-masked clinical trial that will evaluate the efficacy and safety of light-masks in treating and preventing the progression of non-centre-involving DMO. Three hundred patients with non-centre-involving DMO in at least one eye will be randomised 1:1 to light-masks and control masks (with no light) to be used during sleep at night for a period of 24 months. This basic study design and the associated clinical measurements are well-established, having been successfully used in numerous previous clinical trials of DMO. These include visual acuity and retinal thickness measurements using SD-OCT every 4 months, refracted visual acuity, retinal colour photographs, blood pressure, glycosylated haemoglobin (HbA1c), Pittsburgh Insomnia Rating Score
[11] and Epworth Sleepiness Scale
[12] questionnaires to assess sleep at baseline, 12 and 24 months, adverse events and measures of compliance at all 8 study visits over 24 months. Best corrected visual acuity will be repeated at baseline and SD-OCT assessment will be done twice at 12 and 24 months to assess inter-test variability. Participants recruited to the mechanistic evaluation will have additional retinal oximetry, multifocal ERG and microperimetry at baseline and 12 months. Please see visit schedules (Table 
1) and study flow diagram (Figure 
1). At least 15 sites in England and Wales will be participating in this study. Kings Clinical Trials Unit (KCTU) is the co-ordinating centre. The study has been approved by the National Research Ethics Service Committee London - Dulwich (Ref: 13**/**LO**/**0145).

**Table 1 Tab1:** **CLEOPATRA - summary of study assessments**

	Baseline	Week 1	Month 4	Month 8	Month 12	Month 16	Month 20	Month 24 End of trial	
Study Week/Month	Visit 1	Visit 2	Visit 3	Visit 4	Visit 5	Visit 6	Visit 7	Visit 8	Withdrawal
Registration/Demographics	x								
Informed consent	x								
Eligibility form	x								
Randomisation form	x								
Medical history	x								
Concomitant medications	x		x	x	x	x	x	x	x
HbA1c	x				x			x	x
BP	x				x			x	x
Pittsburgh Sleep Quality Index & Epworth Sleepiness Scale	x	x			x			x	x
BCVA (refraction at baseline, 12 and 24 months)	x		x	x	x	x	x	x	x
BCVA (repeated at baseline)^a^	x								
OCT - macular thickness protocol^b^	x		x	x	x	x	x	x	x
Colour photographs - 3-field	x				x			x	x
Mask compliance form		x	x	x	x	x	x	x	x
Adverse events form		x	x	x	x	x	x	x	x
Withdrawal form									x
Additional tests for mechanistic evaluation (n = 30)									
Microperimetry dark-adapted	x				x				
mfERG	x				x				
Retinal oximetry	x				x				

BCVA: best corrected visual acuity; OCT: optical Coherence Tomography; mfERG: multifocal electroretinogram; BP: blood pressure. Note: where an ‘x’ is contained within a field this denotes that the associated data will be collected at the identified time point. ^a^denotes that visual acuity with new refraction should be repeated at baseline. ^b^denotes that OCT scans should be repeated at month 12 and 24 to test for inter-test variability. The average of the two central subfield thicknesses on OCT will be used for the analysis.

**Figure 1 Fig1:**
[figure not shown]
**Flow diagram of the CLEOPATRA trial.** The flow diagram shows the patient flow through the period of the trial and includes the mechanistic evaluation done at one site only.

### Patient recruitment

Patients may be identified from diabetic retinopathy screening programmes and medical retina clinics of the trial sites and its satellite clinics. In addition, patients may be referred by other medical retina consultants from other hospitals to the Principal Investigators (PIs). In order to prevent patients from being subjected to unnecessary trial procedures, it is recommended that potential participants have an SD-OCT done at their clinic visit or at a pre-screening clinic before trial screening procedures are done to ensure exclusion of eyes with centre-involving macular oedema defined as central subfield > 300 μm.

We will report on the numbers of eligible patients informed of the study, the numbers screened and the numbers who were recruited into the study.

Inclusion criteria are:Subjects of either sex aged 18 years or overDiagnosis of diabetes mellitus (type 1 or type 2). Any one of the following will be considered to be sufficient evidence that diabetes is present:Current regular use of insulin for the treatment of diabetesCurrent regular use of oral anti-hyperglycaemic agents for the treatment of diabetesDocumented diabetes by ADA and/or WHO criteriaBest corrected visual acuity in the study eye better than 55 ETDRS letters (Snellen VA 6/24)On clinical exam, retinal thickening due to early DMO not involving the central 1000 μm of the macula characterised by presence of microaneurysm, exudates or oedema and OCT evidence of increased retinal thickness in at least 1 non-central ETDRS zone of ≥320 μm.Previous macular laser, intravitreal steroids or anti-VEGF treatment is permitted provided the last laser treatment was done at least 4 months before date of recruitment or anti-VEGF treatment was done at least 2 months previouslyMedia clarity, pupillary dilation and subject cooperation sufficient for adequate fundus photographsAbility to return for study visitsAbility to give informed consent throughout the duration of the study

Exclusion criteria include:Clinical evidence of centre-involving macular oedema that requires laser treatment within the next 6 months (central subfield on OCT > 300 μm)Macular oedema is considered to be due to a cause other than DMOAn ocular condition is present (other than diabetes) that, in the opinion of the investigator, might affect macular oedema or alter visual acuity during the course of the study (for example, vein occlusion, uveitis or other ocular inflammatory disease, neovascular glaucoma, Irvine-Gass syndrome, and so on).History of treatment for DMO at any time in the past 4 months (such as focal/grid macular photocoagulation, intravitreal or peribulbar corticosteroids, anti-VEGF drugs, or any other treatment) in the study eyeHistory of panretinal scatter photocoagulation in the study eyeActive proliferative diabetic retinopathy in the study eyeA condition that, in the opinion of the investigator, would preclude participation in the studyCorneal scarring, vitreous opacities, severe asteroid hyalosis that would inhibit proper visualisation, inability to be positioned in front of the SD-OCT device, inability to understand the requirements of the imaging, and nystagmusPatients with active insomnia or any other relevant sleep disturbances

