### Randomisation

Randomisation will be via a bespoke 24-hour web-based randomisation system hosted at the King’s Clinical Trials Unit (KCTU). Patients will be randomised at the level of the individual, using the method of minimisation incorporating a random element. The minimisation factors will be HbA1C (< 7.999% (63.89 mmol/mol or below) or ≥8% (69.90 mmol/mol or above), perifoveal or parafoveal location of baseline zone of increased retinal thickness of ≥320 μm (parafoveal zone 2 to 5 or perifoveal zone 6 to 9) and study site. If both parafoveal and perifoveal zone thickening co-exist, it will be categorised as parafoveal.

Patients may only be randomised into the study by an authorised member of staff at the study site as detailed on the delegation log. Participants may only be randomised into the study once.

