### Outcomes

The primary efficacy measure is the difference between arms in the change from baseline in absolute retinal thickness at the zone of maximum thickness as determined by OCT at 24 months.

The secondary efficacy parameters at 12 and 24 months are:

Efficacy parameters:I.Difference between arms in the change from baseline in absolute thickness at the zone of maximum thickness as determined by OCT at 12 months.II.Other measures include: Difference between arms in the change in retinal thickness in the 9 ETDRS zones (parafoveal zones 2-5 and perifoveal zones 6-9) and macular volume.Difference between arm in morphological characteristics of macular thicknessDifference between arms in the mean change in visual acuity.Difference between arms in the proportion of centre-involving macular oedema within 24 months.Difference between arms in the time to occurrence of centre-involving macular oedema.Difference between arms in the proportion requiring macular laser or antiVEGF treatment.Difference between arms in the proportion of participants that show progression of retinopathy as measured by the ETDRS severity levels and microaneurysm turnover.Compliance rates in the light mask arm.

II. Assessment of Safety Parameters {XE “6.2 Procedures for Assessing Efficacy Parameters”}Difference between arms in the measures of sleep disturbance in terms of daytime sleepiness and insomnia.Difference between arms in ocular and systemic adverse events and serious adverse events.

III. Assessment of Mechanistic Parameters {XE “6.2 Procedures for Assessing Efficacy Parameters”}Change in P1 and N1 amplitudes and peak time in multifocal ERG after supplemental oxygenChange in retinal sensitivity in scotopic microperimetry after supplemental oxygen.To determine differences in change in P1 and N1 amplitudes and peak time in multifocal ERG after light-masks and dummy masks at 12 months.To determine differences in change in retinal sensitivity in scotopic microperimetry after light-masks and dummy masks at 12 months.To correlate the changes induced by light-masks and oxygen supplementation on retinal sensitivity using oximetry.

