### Statistical analysis

The primary outcome will be analysed using a two-sided test from a linear mixed effect model for repeated measures across visits, which will enable a comparison between participants receiving light-masks (active) and control masks, with covariates for each follow-up visit of baseline, randomisation stratifier and arm, and with a random participant effect at each visit with unstructured covariance matrix. The primary time-point will be 24 months. The 20% allowance for dropout (trial withdrawal) is based on 18% early non-compliance observed in the pilot study and we would expect a reasonable proportion of non-compliers to provide primary time-point and intermediate visit outcome information for this analysis.

We expect the DMEC would want to monitor study power and we would regularly provide information such as non-compliance, withdrawal, and variability of the primary outcome with increasing certainty as increasing proportions of the participants pass each of the 4-monthly measurement points.

The detailed statistical analysis plan will include an additional sensitivity analysis involving all randomised participants (intention to treat strategy) examining the influence on the primary outcome analysis of opposing optimistic and pessimistic scenarios for the intervention effect in those withdrawing in each arm. We will adopt the complier average causal effects (CACE) analysis (under a missing at random assumption) as recommended and outlined by Dunn *et al*.
[15].

Linear mixed effect models for repeated measures (as specified above for the primary outcome), logistic regression, and stratified Cox regression, will also be undertaken to analyse secondary and mechanistic outcomes of continuous, binary and time to occurrence type respectively. Differences will be considered significant at *P* < 0.05. Differences between the groups will be estimated with 95% confidence intervals. Repeated measure analyses (linear mixed effects models) will be used to document trends over time.

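### Eyes with prior anti-VEGF may enrol, but prior DMO treatment is not in the minimisation or the stated mixed-model covariates, and the centre-involvement outcomes do not separate first onset from recurrence

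*Protocol article*

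**What the plan says.** All references are to the protocol article.

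- **Patient recruitment, inclusion criteria.** The target is early DMO that spares the central macula, but "Previous macular laser, intravitreal steroids or anti-VEGF treatment is permitted" once a minimum interval has passed. The exclusion criteria rule out only recent treatment of the study eye: "History of treatment for DMO at any time in the past 4 months". Older treatment is not limited.
- **Background.** On anti-VEGF: "Newer treatment options of injections of vascular endothelial growth factor (VEGF) inhibitors are also available but only for centre-involving DMO". On laser: "Laser photocoagulation may be performed for non-central clinically significant macular oedema". No indication is given for intravitreal steroid.
- **Randomisation.** "The minimisation factors will be HbA1C" (split at 8%), parafoveal or perifoveal location of the thickened zone, and study site.
- **Statistical analysis.** The primary mixed model is fitted "with covariates for each follow-up visit of baseline, randomisation stratifier and arm". Continuous secondary outcomes use the same form of model. Logistic and stratified Cox regression are named for binary and time-to-event outcomes, without their covariates or strata.
- **Outcomes.** The secondary outcomes include the proportion with centre-involving oedema within 24 months and "Difference between arms in the time to occurrence of centre-involving macular oedema". Neither distinguishes a first occurrence from a return.
- **Objectives.** The secondary aim is to prevent progression of non-centre-involving DMO.

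**The concern.** Read together, the Background and the inclusion criteria imply that the trial may enrol two kinds of eye. Some have never had central oedema. Others have had it, were given anti-VEGF, and now have a central subfield at or below the entry limit of 300 μm. If the second kind thickens centrally during follow-up, the event is a return of earlier disease, whereas the stated aim concerns progression from non-central disease. The Discussion also expects the control arm to describe the natural history of non-centre-involving DMO, and a control arm that mixes the two kinds does so less clearly.

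Two things are at stake. The first is what the centre-involvement results mean: the event rate would be a blend of unknown composition. The second is precision. Prior treatment may predict thickness change, but it is neither balanced by design nor in the stated covariate list, although the eligibility check already requires it to be known.

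**Working it through.** **1. The plan's own figure.** Inputs from Sample size calculation: difference 15 μm, SD 35.7 μm, two-sided 5%, 90% power, 20% dropout.

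n per arm = 2 × (1.960 + 1.282)² × 35.7² / 15² ≈ 119.03, rounded up to 120. The total is 240, and 240 / 0.8 = 300. Power at 120 per arm is 90.2% by the normal formula and 90.0% by the noncentral t. The stated sample size reproduces exactly.

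**2. Gain from adjustment.** The documents give no prevalence p of prior treatment and no shift D in mean thickness change between treated and untreated eyes. Both are assumed here: p from 10% to 50%, and D from 5 to 20 μm, where D is the difference left after the planned covariates.

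- Variance explained: R² = p(1 − p)D² / 35.7²
- Residual SD = 35.7 × √(1 − R²)
- 95% limit of chance imbalance between arms of 120: 1.96 × √(2p(1 − p)/120)
- Resulting movement of the unadjusted estimate: imbalance × D

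| p | D (μm) | R² | Power, adjusted | 95% imbalance (points) | Movement (μm) |
|---|---|---|---|---|---|
| 10% | 5 | 0.002 | 90.3% | 7.6 | 0.38 |
| 10% | 20 | 0.028 | 91.0% | 7.6 | 1.52 |
| 30% | 10 | 0.017 | 90.7% | 11.6 | 1.16 |
| 30% | 20 | 0.066 | 92.0% | 11.6 | 2.32 |
| 50% | 5 | 0.005 | 90.4% | 12.7 | 0.63 |
| 50% | 20 | 0.078 | 92.4% | 12.7 | 2.53 |

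A much larger gain needs a much larger shift. At p = 40% and D = 40 μm, R² = 0.24 × 1600 / 1274.5 = 0.30 and power is about 97%. That shift exceeds the planning SD itself.

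**3. Make-up of the centre-involvement events.** Let q be the share of eyes with earlier central involvement and r their risk of recurrence. Take 30% as the control risk in the other eyes. This borrows the 12-month progression figure in the Background, although the outcome runs to 24 months. q (10% to 50%) and r (30% to 60%) are assumptions.

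Share of control events that are recurrences = qr / [(1 − q) × 0.30 + qr].

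- q = 10%, r = 30%: 0.03 / 0.30 = 10%
- q = 20%, r = 45%: 0.09 / 0.33 = 27%
- q = 50%, r = 60%: 0.30 / 0.45 = 67%

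Over the same range, an odds ratio of 0.50 within each type of eye would appear as 0.50 to 0.53 without adjustment. The effect estimate is hardly diluted, but the composition of the events could vary widely and the planned outcomes would not show it.

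**The case against.** The strongest reply is that the plan makes no error here. Adjusting for baseline thickness and the balancing factors is a coherent choice, and one more candidate covariate is a preference. Eyes with a central subfield above 300 μm are excluded at entry, so centre involvement during the trial is a genuine event whatever the history. The article also defers detail to a statistical analysis plan that is not at hand. Much of this stands, and it rules out several stronger readings that a reader might infer:

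- **That leaving out the covariate makes recurrence count as progression.** It does not. The counting follows from eligibility and the outcome definition. Minimising on prior treatment or adjusting for it would balance recurrences or account for them, but they would still be counted.
- **That every previously treated eye has had central oedema.** The Background supports this for anti-VEGF only. It allows laser for non-central disease and is silent on steroid.
- **That the logistic and Cox models omit prior treatment.** Their covariates and strata are not stated, so no omission is shown.
- **That the trial is biased or underpowered.** Randomisation keeps the comparison unbiased in expectation, the confidence interval already allows for chance imbalance, and the 90% power is correct.
- **That later thickening in treated eyes is treatment wearing off.** The intervals at entry are minimums. Treatment could have been much earlier, and the documents say nothing about the cause.

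The reply does not dispose of two points. The minimisation factors and the primary covariates are stated, not deferred, and prior treatment is in neither list. The centre-involvement outcomes also cannot answer the progression question cleanly for eyes that, on the plan's own account, have already had the event.

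**Conclusion.** The concern holds as a matter of precision and interpretation. For the primary outcome the benefit of adjustment is small: 90.3% to 92.4% power against about 90%, and protection against a chance movement of about 0.4 to 2.5 μm. For the centre-involvement outcomes the treatment effect is little changed, but recurrences could form anywhere from 10% to 67% of control events. All these ranges rest on assumed prevalence, shift and recurrence risk. The inference about earlier central disease rests on the Background's statement about anti-VEGF and applies only to study eyes treated with it. The change is still worth making because it is cheap, uses information already required at entry, and is far more credible if specified before the data are seen.

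**What to change.** 1. Pre-specify prior DMO treatment of the study eye as a baseline covariate in the mixed models. Suggested levels are none, laser only, and anti-VEGF or steroid, merged if sparse.
2. Include it among the adjustment factors of the logistic models and the strata or adjustment factors of the Cox model.
3. Pre-specify a supportive analysis of both centre-involvement outcomes in eyes with no prior anti-VEGF. This subgroup is defined before randomisation, so the comparison within it remains randomised. It may still hold some eyes with earlier central disease treated in other ways, so it narrows the mixture but does not guarantee first onset.

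The cost is one or two degrees of freedom per visit and one smaller supportive analysis. Eligibility, visits and sample size do not change.

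Separately, the inclusion criteria give a minimum of 2 months since anti-VEGF, while the exclusion criteria rule out any DMO treatment of the study eye within 4 months. These passages must be reconciled.
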